### Inclusion criteria

We shall include participants who meet the following criteria: road-traffic police officer, medical intern doctor/nurse, medical student enrolled in Bachelor of medicine and Bachelor of Surgery in clinical years (3rd or 5th) who completed or currently is completing the surgical/traumatology clinical rotation, allied health professional trainee enrolled in Bachelor of Nursing Sciences or Bachelor of Clinical Medicine degree program and is involved in the care of the injured patients or attached to the accident and emergency department during the study period.

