### Statistical analysis

The data will be exported from REDCap to Stata version 15.0 for analysis (StataCorp. 2017. Stata Statistical Software: Release 15. College Station, TX: StataCorp LLC).

We shall test the data for normalcy using the Shapiro–Francia test and normal histogram curves at 95% CI, regarding *P*<0.05 as statistically significant.

If the data are normally distributed, the difference in pretraining and post-training mean scores will be compared using one way analysis of variance (ANOVA) test otherwise nonparametric Friedman test will be used to compare the scores as a measure of knowledge retention, assuming a null hypothesis of no difference. Box plots will be used for data presentation to offer a succinct visual summary of data distribution.

Furthermore, we shall perform Wilcoxon signed rank nonparametric test to examine the difference in the effect the training has on MCQ scores of the various cadres of participants aggregated (3rd year, 5th year, and interns). The median scores for various groups and their corresponding interquartile range will be reported.

The statistical difference in rank sums regarding desirability and relevance of various course themes will be compared between participating cadres using a nonparametric Kruskal–Wallis (H) test.

Lastly, time series regression (ARIMA) models will be used to test for autocorrelation trends in MCQ performance over the study period for the various medical trainee groups.

All the analyses will be performed using Stata 15.0. (StataCorp. 2017. *Stata Statistical Software: Release 15.* College Station, TX: StataCorp LLC); at 95% CI, regarding a 2-tailed *P*-value <0.05 as statistically significant.

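### The signed-rank test named for the cadre analysis measures pre/post change within one group, so a between-cadre difference in training effect is not tested

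*Protocol article*

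**What the plan says.** The Statistical analysis section of the protocol article lists five analyses.

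- **Overall pre/post:** "the difference in pretraining and post-training mean scores will be compared using one way analysis of variance (ANOVA) test", with the Friedman test if the data are not normal. No cadre factor is named.
- **Cadres, MCQ:** a "Wilcoxon signed rank nonparametric test to examine the difference in the effect the training has on MCQ scores of the various cadres". The groups are given as "cadres of participants aggregated (3rd year, 5th year, and interns". The reporting attached to it is descriptive: "The median scores for various groups and their corresponding interquartile range will be reported".
- **Cadres, ratings:** rank sums "regarding desirability and relevance of various course themes will be compared between participating cadres using a nonparametric Kruskal–Wallis (H) test".
- **Time series:** ARIMA models to "test for autocorrelation trends in MCQ performance over the study period for the various medical trainee groups".
- **Normality:** the Shapiro–Francia test and histograms.

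Specific objectives asks for pre- versus post-course scores among medical trainees, and Hypotheses states a null of no pre/post difference. Neither names a contrast between cadres. Inclusion criteria also admits any "allied health professional trainee enrolled in Bachelor of Nursing Sciences or Bachelor of Clinical Medicine degree program" who is involved in injury care or attached to the emergency department.

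**The concern.** Comparing the training effect across third-years, fifth-years and interns means comparing change in three independent groups. The signed-rank test takes one set of paired differences and asks whether they centre on zero. It has no term for a difference between groups.

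If it is run in each cadre, the output is three separate P-values. A reader may then take a significant result in one cadre and a non-significant one in another as a difference in effect, or take three significant results as sameness. Neither inference is sound. If it is run on all cadres pooled, the output says nothing about cadres.

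The three listed groups also give no visible place to Bachelor of Nursing Sciences and Bachelor of Clinical Medicine students. Source of data and study settings counts them as medical trainees, and Participant recruitment workflow has interns and medical trainees sit the MCQ. Inclusion criteria attaches the third and fifth years to the medicine and surgery degree.

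**Working it through.** **1. Does another listed analysis answer the question?** No. ANOVA/Friedman compares pre with post. Kruskal–Wallis is an independent-groups test between cadres, but it is assigned only to desirability and relevance. ARIMA concerns autocorrelation over calendar time. The cadre contrast on MCQ change rests on the signed-rank test alone.

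**2. The plan's own figure.** Only the total is stated. With N = 1500, z = 1.96, p = q = 0.5 and E = 0.05, n = N z²pq / [E²(N−1) + z²pq] = 305.996, against 307 stated. Then 307 × 1.41 = 432.87, so 433 is reproduced. Nothing is sized for cadres.

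**3. Assumptions.** The article gives no cadre sizes, expected gain or SD. I take 433 trainees in three cadres and an SD of change of 15 points; an SD of 15 at each time with correlation 0.5 gives √[2 × 15² × (1 − 0.5)] = 15. Scores move in 5-point steps because the MCQ has 20 items. Tests are two-sided at 0.05.

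**4. Equal true gains: how often do three separate tests disagree** (some significant, some not)? Simulation, 1,500 to 2,000 trials per cell, Monte Carlo standard error at most about 1.3 points:

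| Cadre sizes | Gain 3 | Gain 5 | Gain 10 |
|---|---|---|---|
| 144/144/145 | 68% | 7% | 0% |
| 200/150/83 | 74% | 18% | 0% |
| 300/80/53 | 86% | 48% | under 1% |
| 300/100/33 | 89% | 60% | 5% |

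Kruskal–Wallis on the change scores rejects in about 5% throughout, as it should.

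Hand check: the power of one signed-rank test is roughly Φ(gain × √(3n/π)/15 − 1.96), and P(disagree) = 1 − p₁p₂p₃ − (1−p₁)(1−p₂)(1−p₃).
- Equal thirds, gain 3: p ≈ Φ(2.345 − 1.96) = 0.65, so 1 − 0.65³ − 0.35³ = 1 − 0.275 − 0.043 = 0.68.
- 300/100/33, gain 5: p ≈ 1.000, 0.903 and 0.465, so 1 − 0.420 − 0 = 0.58, close to the simulated 60%.

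**5. Truly different gains of 5, 10 and 15 points, equal cadres:**

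| SD of change | All three signed-rank tests significant | Kruskal–Wallis on change significant |
|---|---|---|
| 10 | 100% | 100% |
| 15 | 98% | 99.7% |
| 20 | 82% | 97% |

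Hand check at SD 15: the weakest cadre has power Φ(3.909 − 1.96) = 0.974 and the other two about 1, so the product is about 0.97.

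At SD 15 with unequal cadres, all three tests are significant in nearly 100% of trials if the smallest gain falls in the largest cadre. The figure drops to 83%, 65% and 46% for the three unequal splits if it falls in the smallest cadre. Kruskal–Wallis on change detects the difference in at least 97% in every split.

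**The case against.** The sentence is ambiguous. It does not say between cadres, it includes the word aggregated, and it is followed by medians per group. The next sentence does say between cadres and names Kruskal–Wallis, so the authors may have meant only a pre/post test within each cadre. For that the signed-rank test is valid, and the defect is loose wording. This stands as a possible reading, but the stated aim is a difference in effect across cadres, and on either reading no listed analysis tests it.

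The disagreement rate also depends heavily on the assumed gain. Three points is less than one MCQ item, and at 10 points disagreement nearly vanishes. This stands too, which is why a range is shown. A large gain does not rescue the test, because it then tends to hide real differences.

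Three stronger readings are tempting and not supported.
- **That cadre conclusions would follow group size rather than effect.** With equal cadres the tests still disagree in 68% of trials at 3 points, so much of it is chance at low power. Nor does the article say it will infer cadre differences from significant versus non-significant results.
- **That nursing and clinical medicine students would be dropped.** The article does not say so. Nurse interns fit the intern group, and the overall pre/post analysis excludes no trainee. What holds is that degree students in these programmes have no stated cadre.
- **That the main result is compromised.** No objective, hypothesis or sample-size input concerns cadres.

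A separate analysis plan may exist, but the article names this test for this purpose, so the point concerns what it states and not an omission.

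**Conclusion.** The point holds as a mismatch between the named test and its stated aim in a secondary analysis. It deserves correction and does not threaten the main comparison.

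The mismatch itself needs no assumptions. Its size does: with 433 trainees and an SD of change of 15, separate tests can suggest a cadre difference where none exists, often at a 3-point gain, in a minority to a majority of trials at 5 points depending on how unequal the cadres are, and rarely at 10. They can also conceal a threefold difference in gain when every cadre is large enough to reach significance. A direct test on change scores avoids both errors under the same assumptions.

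**What to change.** 1. State that the signed-rank test is for pre/post change within each cadre only.
2. For the between-cadre question, compute each participant's change (post minus pre) and compare it across cadres with Kruskal–Wallis, which the plan already uses for the ratings. A cadre-by-time interaction is an equivalent choice; with two time points it amounts to a one-way ANOVA on the change scores.
3. Report each cadre's change with its 95% CI, and state that cadre differences will not be inferred from significant versus non-significant within-cadre results.
4. Make Bachelor of Nursing Sciences and Bachelor of Clinical Medicine trainees a stated group in this comparison.
5. If only within-cadre tests were intended, reword the sentence to say so and drop the claim to examine a difference in effect. The trainee groups still need completing.

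The cost is wording. No new data or participants are needed, since both MCQ scores are collected and eligibility already depends on the degree programme. Recruitment was due to end before the article appeared, so the change should be dated and should say whether results had been seen.

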### Specific objectives

To compare the pre-RTTDC and post-RTTDC training scores amongst medical trainees.To determine the relevance and acceptability to promulgation of RTTDC amongst medical trainees and traffic law enforcement professionals in Ugandan rural level III trauma centers.

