### Sample size estimation

According to the respective hospital administrators, a total of 1500 medical trainees had been received at the three participating hospitals during the academic year 2018/2019, which preceded the study. Using the hypergeometric formula in equation 1 for determining sample size in smaller populations,

(1)
$$n=\frac{Nz^{2}\mathrm{pq}}{\left[E^{2}\left(N-1\right)+z^{2}\mathrm{pq}\right]}$$

where:

*N* (population size) =1500

Z=1.96 assuming 95% CI.

P and Q are population proportions that will approve or disapprove the promulgation of rural trauma team development training, each assumed to be 50% since these proportions are unknown

E=value of accuracy of the sample proportions (alpha= 0.05) at 95% CI

*n* (sample size)=307. Since, we plan to retain this same cohort of trainees after 3 months of follow-up for purposes of their incorporation into real-world rural trauma teams during the second phase of the project which will run for the next 4 years from the time of postcourse evaluation, and with a projected 10.25% annual loss to follow-up and nonresponse, we shall add 41% to increase internal validity for the entire 4-year period, thus the final minimum sample size for medical trainees will be 433.

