### Sampling methods

For proportionate representation, the proportion ‘p’ will be computed as shown in equation 2, depending on the number of medical trainees each hospital received during the year that preceded the study.

(2)
$$p=\mathrm{sample}\left(n\right)x\frac{100}{\mathrm{Population}\left(N\right)},$$

This means that ~26.7% of each hospital’s annual trainees intake will be recruited, resulting in 321 participants from Kiryandongo, 65 from Jinja, and 47 from Hoima regional referral hospitals.

For the case of law enforcement professionals, the selection will be purposive where the regional police in-charge of traffic will be asked to nominate 22 participants, which is approximately the average number of serving officers at the headquarters for each region, totaling to 66, targeting police stations on main highways leading to the respective municipalities where the study sites are located. Those who consent to participate will then be randomly assigned to join the medical trainee teams. The assignment will be that only 1–2 traffic officers attend a particular training until the required number is attained so as not to strain the police workforce.

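### Trainees follow hospital intake across sites but police are split equally, so the unstratified Kruskal–Wallis comparison of ratings would pass part of any site difference to the police–trainee contrast

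*Protocol article*

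**What the plan says.** Sampling methods sets two rules for spreading participants over the three hospitals.

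- Trainees are allotted "depending on the number of medical trainees each hospital received during the year that preceded the study", "resulting in 321 participants from Kiryandongo, 65 from Jinja, and 47 from Hoima regional referral hospitals".
- For police, the officer in charge of traffic in each region "will be asked to nominate 22 participants, which is approximately the average number of serving officers at the headquarters for each region, totaling to 66".

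Both groups rate the course. The second specific objective is "To determine the relevance and acceptability to promulgation of RTTDC amongst medical trainees and traffic law enforcement professionals in Ugandan rural level III trauma centers". Participant recruitment workflow has every study subject fill in the acceptability and relevance form at the end of Day 2.

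For these ratings, Statistical analysis names one test: "desirability and relevance of various course themes will be compared between participating cadres using a nonparametric Kruskal–Wallis (H) test". It mentions no stratification or adjustment for hospital and does not list the cadres for this test. The cadres listed nearby (3rd year, 5th year, interns) belong to the sentence on MCQ scores.

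Study strengths and limitations does mention confounding from between-group differences, but relies on the time series models to limit it. Statistical analysis applies those models to trainees' MCQ performance, not to the ratings.

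**The concern.** With these quotas, nearly three quarters of trainees but only a third of police would be at Kiryandongo. A test that pools the hospitals cannot tell a cadre difference from a site difference. If participants at Kiryandongo rated the course higher or lower than those elsewhere, police and trainees would appear to differ even if they agreed within every hospital. A real difference could equally be masked.

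This is bias in the contrast, not a matter of precision. Allowing for correlation within training sessions would change the standard errors but leave the bias. If a site shift were general rather than specific to one theme, it would move many of the rated themes in the same direction, and the resulting spurious differences would look like a consistent pattern.

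**Working it through.** **The plan's own counts.** The finite-population formula in Sample size estimation gives 1500 × 1.96² × 0.25 / (0.05² × 1499 + 1.96² × 0.25) = 1440.6 / 4.708 = 306.0 (stated 307). Adding 41% gives 307 × 1.41 = 432.9, the stated 433. The site figures agree: 321 + 65 + 47 = 433 and 3 × 22 = 66. (The quoted sampling fraction of about 26.7% matches 400/1500; 433/1500 is 28.9%. This does not affect the site shares.)

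**Site shares (Kiryandongo / Jinja / Hoima).**
- Trainees: 321/433, 65/433, 47/433 = 74.1 / 15.0 / 10.9%.
- Police: 22/66 each = 33.3 / 33.3 / 33.3%.
- Police minus trainees: −40.8 / +18.3 / +22.5 points.

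**Bias in the mean.** Let ratings at Kiryandongo differ from the other two sites by d, with no cadre effect. The expected police–trainee difference is (0.333 − 0.741) × d = −0.408d, so about 41% of the site difference is passed to the contrast.

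**Effect on the test.** The article gives no site difference in ratings, so d is assumed. Other assumptions: 433 trainees and 66 police at the stated site counts; a 5-point item with underlying frequencies 2/5/13/40/40%; three equal trainee cadres unrelated to site; no cadre effect within site; two-sided α = 0.05; 2000 runs per setting (standard error about 0.5 points near 5%). False-positive rates, %:

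| Kiryandongo shift (SD) | Kruskal–Wallis, police + 3 trainee cadres | Kruskal–Wallis, police v trainees | Site-stratified rank test, police v trainees | Kruskal–Wallis, trainee cadres only |
|---|---|---|---|---|
| 0 | 5.5 | 5.4 | 5.3 | 4.7 |
| 0.2 | 6.1 | 8.2 | 4.3 | 5.0 |
| 0.3 | 9.3 | 12.7 | 4.5 | 5.5 |
| 0.5 | 19.4 | 28.4 | 5.7 | 5.3 |
| 0.8 | 38.0 | 54.5 | 4.1 | 5.6 |

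A separate simulation at shifts 0 / 0.2 / 0.3 / 0.5 gave 5.4 / 6.5 / 8.7 / 18.1% for four cadres and 4.8 / 8.2 / 12.3 / 28.6% for police versus trainees. There the stratified rank test held 4.7–5.5% in both its two-group and four-cadre forms. A 3-point item behaved similarly (four cadres: 6.8 / 8.3 / 16.5% at 0.2 / 0.3 / 0.5 SD).

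**Is the quota mismatch the cause?** With the 66 police spread like trainees (49/10/7), the unstratified police-versus-trainee test stayed at 3.8–4.7% for shifts of 0.3–0.8 SD. The inflation therefore comes from the two different allocation rules.

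**More cadres.** Inclusion criteria also admits nursing and clinical medicine trainees. With five trainee cadres plus police, the rate was 8.0% at 0.3 SD and 14.1% at 0.5 SD.

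**The case against.** **No site difference is shown.** A reader might infer that ratings do differ by hospital and will be misreported. The article does not support this. It describes the hospitals as alike in role, keeps the course unmodified, and has three trainers deliver every session in similar rooms. This stands, and it makes the point conditional. Equality is not assured either. The co-trainers are described as residents on rotation at the participating hospitals, which fits uneasily with one constant team. At the quotas, police would be 22/343 = 6% of participants at Kiryandongo, 22/87 = 25% at Jinja and 22/69 = 32% at Hoima, so team composition would differ.

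**Police may not be in the test.** The sentence does not define its cadres, so their inclusion is inferred from the second objective and the workflow. Without police this mechanism disappears: trainee-only comparisons kept their level, given a cadre mix unrelated to site.

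**The two-group figures are not for the planned test.** Correct. The plan names one test across cadres, for which the inflation is smaller and falls further as trainee cadres are added.

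**The equal split is a target.** Sampling methods allows only 1–2 officers per training. If sessions were filled with about 28 trainees and 2 officers, Kiryandongo would need 321/28 ≈ 11.5 sessions, Jinja 2.3 and Hoima 1.7. That allows at most about 23/5/4 officers, close to the trainee mix, and the unstratified test then held 4.2–5.5%. But the article also gives an average of 12 sessions per site, which accommodates 12–24 officers, and continues until the number is reached. Both readings are open.

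**Importance.** A reader might take the contrast to be what the sample was sized on. It is not: 433 rests on one approval proportion among trainees, and the police number was set by nomination.

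**It belongs in an analysis plan.** Detail left out would be no finding. Here the article itself names an unstratified test and sets the quotas that undermine it.

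**Conclusion.** The point holds conditionally. Three things are needed: police are among the cadres compared, police attendance is near 22 per region, and ratings differ between Kiryandongo and the other hospitals. The first is implied, the second is a stated target, and the third is assumed.

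Where all three hold, the named test would report about 41% of the site difference in mean rating as a police–trainee difference. For assumed shifts of 0.2 / 0.3 / 0.5 SD, the false-positive rate is about 6.5 / 9 / 18% with four cadres and about 8 / 12 / 28% for police versus trainees. With negligible site differences there is no material problem. The issue is confined to a secondary comparison under the second objective. It does not reach the MCQ analysis, the sample size or, on the assumption above, comparisons among trainee cadres. It is still worth correcting, because the association comes from the plan's own quotas and the remedy is cheap.

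**What to change.** In Statistical analysis, define the cadres for the comparison of desirability and relevance ratings, state that police are included, and stratify the comparison by hospital. Either of these would do:

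- a multi-group stratified rank test (van Elteren, or the Cochran–Mantel–Haenszel row-mean-scores form); or
- an ordinal logistic model for each rating, with cadre and hospital (three levels) as fixed terms, reporting the cadre contrast from it.

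If police are not meant to be in this test, the article should say so, and this point then falls away.

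The site quotas need not change. Recruitment is by hospital, so site is known for every participant. No new data are needed, and the change can be made after recruitment has ended. The cost is some power if sites do not differ: for a 0.4 SD police–trainee difference with no site effect, simulated power fell from 78% (unstratified) to 73% (stratified).

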**Methods::**

Muticenter interrupted time series of prospective interventional trainings, using the rural trauma team development course (RTTDC) model of the American College of Surgeons. A team of surgeon consultants will execute the training. A prospective cohort of participants will complete a before and after training validated trauma related multiple choice questionnaire during September 2019-November 2023. The difference in mean prepost training percentage multiple choice questionnaire scores will be compared using ANOVA-test at 95% CI. Time series regression models will be used to test for autocorrelations in performance. Acceptability and relevance of the training will be assessed using 3 and 5-point-Likert scales. All analyses will be performed using Stata 15.0. Ethical approval was obtained from Research and Ethics Committee of Mbarara University of Science and Technology (Ref: MUREC 1/7, 05/05-19) and Uganda National Council for Science and Technology (Ref: SS 5082). Retrospective registration was accomplished with Research Registry (UIN: researchregistry9490).

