### Training procedure, team construct, and course implementation

On average 12 (6–24) training sessions will be conducted per site between 28th of September 2019 and 28th of November 2023. Cohorts of participants will be enrolled every after 3 months to strike a balance between the average duration of surgical internship deployment by the Ugandan ministry of health which lasts 1–5 months, and the surgery clinical rotations for medical students which lasts 2 months. Furthermore, the effects of the training are presumed to ‘decay’ after this period and the authors project to realize the targeted sample size based on the 3 months interval. However, permission will be sought from the ethical committee to extend the study in case the target sample is not obtained during the approved duration of the study. The mode of delivery and content of the RTTDC training will not be modified. The training will be advertised by hospital administrators and class representatives and eligible participants will be recruited based on first come first serve. The training dates will be selected to suit the designated days for clinical grand rounds and/ or continuous professional development sessions so as not to interfere with the university and hospital daily schedules. The investigators will use student unique numbers from university hospital administrators’ database to randomly assign recruited participants into teams and to ensure that each participant is recruited once. The participating law enforcement professionals who will show up for the training will pick ballot papers randomly to be assigned to the already created medical trainee teams. The chief trainer will be a chief surgeon (HL) who attended the RTTDC instructor course. The surgeon will coach two co-trainers who are master of surgery residents undertaking a traumatology rotation, at the participating hospitals to make a total of three trainers. Since the program is aimed at capacity building, and residents directly supervise interns in Uganda, the research and ethics board approved training of residents as opposed to consultants not to over strain the skeleton specialized staff at the study sites. Interns and residents contribute to 75% of the health workforce in public hospitals in Uganda^8^. The program will be designed for two days, targeting 30 participants with a trainer: trainee ratio of 1:10, which is the maximum permissible for each training session according to the committee on trauma of the American college of Surgeons. For each team task, participants will be grouped into teams of five to role play a surgeon, surgeon assistant/intern, an anesthesiologist/anesthetic assistant, an allied health professional (emergency room nurse/laboratory/imaging personnel), and a rescue police (representing paramedics in Uganda’s settings).

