### Study strengths and limitations

There will be some limitations in this study. First, our trauma team simulation with traffic police and students in medical training could arguably differ from the physician-led emergency medical teams in affluent Western countries, consequently limiting the generalizability of our results to LMICs. Secondly, regarding training for police, we hope to emphasize the key communication aspects of evacuation and prehospital safe transportation of injured patients to hospitals. As such, we shall not assess the trauma knowledge based MCQ for law enforcement participants on assumption that they have no pre-existing clinical exposure but information on their trauma nontechnical skills and applicability of the gained knowledge to their work environment will be obtained. Furthermore, medical trainee participants’ knowledge could change with time irrespective of the intervention but we hope that having multiple interrupted time series of intervention sessions at multiple study sites and using time series autoregression models will overcome this obstacle in addition to limiting confounding due to between group differences^38^. Lastly, the mean difference in prepost training MCQs for medical trainees might only depict knowledge improvement which does not necessarily transform to clinical skills that impact patient outcomes. However, the authors plan to transfer this classroom knowledge into clinical practice in a cluster randomized controlled trial to determine whether the apparent knowledge changes during the training are not due to other interventions, impact on clinical time efficiency, and patient outcomes in our constrained resource context.

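### The time-series analysis tests autocorrelation in MCQ scores, which neither estimates nor tests change over the study period, yet the protocol relies on it to deal with change over time

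*Protocol article*

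**What the plan says.** The last analysis in the Statistical analysis section of the protocol article reads "time series regression (ARIMA) models will be used to test for autocorrelation trends in MCQ performance over the study period for the various medical trainee" (by group). The Methods paragraph of the abstract gives the same target: "Time series regression models will be used to test for autocorrelations in performance". The significance rule is "regarding a 2-tailed *P*-value <0.05 as statistically significant".

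Under Study strengths and limitations, the protocol concedes that medical trainee "participants’ knowledge could change with time irrespective of the intervention". It then hopes that repeated sessions at several sites and "using time series autoregression models will overcome this obstacle".

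The section on training procedure sets the length of the series: "Cohorts of participants will be enrolled every after 3 months" and "On average 12 (6–24) training sessions will be conducted per site", between 28 September 2019 and 28 November 2023. It also says that each participant is recruited once, so successive cohorts are different people.

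**The concern.** The only test target stated, in both places, is autocorrelation. The purpose stated in the limitations section is to deal with change in knowledge over time. These are different questions. The null of an autocorrelation test is that successive cohort scores are serially uncorrelated. The null for change over time is that mean score, or mean gain, is constant across session dates.

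Neither result of the planned test answers the second question. A non-significant result is compatible with a moderate drift in pre scores or in gain. A significant result could come from a drift, a step or real dependence between neighbouring cohorts, and it has no size in MCQ points. The protocol would then claim to have handled change over time without having estimated it.

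**Working it through.** **Inputs from the protocol.** Enrolment runs for 50 months at 3-month spacing. Cohorts at months 0, 3, …, 48 give 17 time points. Sessions per site average 12, range 6 to 24. Alpha is 0.05, two-sided. The minimum number of trainees is 433. The protocol gives no power or detectable drift for this analysis, so there is no stated figure to reproduce.

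**Assumptions, not in the protocol.** Cohort means are independent, and drift is linear, with total change D from first to last cohort in SDs of a cohort mean. The autocorrelation test is a lag-1 Ljung-Box test on the raw series.

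**Scale, also assumed.** Three equal cadres over 17 cohorts give 433 / 17 / 3 ≈ 8.5 trainees per point. With an individual SD of 15 points, the SD of a cohort mean is 15/√8.5 ≈ 5.1 points (3.4 to 6.9 for an individual SD of 10 to 20). So 2 SD is about 10 points, or two items on the 20-item test, and 4 SD is about 21 points.

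**Slope test.** The non-centrality is D/(n−1) × √S, with S = n(n²−1)/12.
- n = 17, D = 2: S = 408, so 2/16 × 20.20 = 2.52, and power is 66%.
- n = 12, D = 3: S = 143, so 3/11 × 11.96 = 3.26, and power is 84%.

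**Lag-1 test.** It rejects when |r₁| exceeds √[3.84(n−1)/(n(n+2))], which is 0.436 for n = 17 and 0.502 for n = 12. With b = D/(n−1) and A the sum of products of neighbouring centred time values, the typical r₁ is about [A·b² − (n−1)/n] / [S·b² + (n−1)].
- n = 17, D = 2 (A = 336): (5.25 − 0.94)/(6.38 + 16) = 0.19, well below 0.436.
- n = 17, D = 4: (21.0 − 0.94)/(25.5 + 16) = 0.48, just above 0.436.
- n = 12, D = 3 (A = 107.25): (7.98 − 0.92)/(10.64 + 11) = 0.33, below 0.502.

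Unremoved drift therefore does create positive autocorrelation, but too little to cross the threshold until the drift is large. At n = 6 even a perfect straight line gives r₁ = 8.75/17.5 = 0.50, below the threshold of 0.633.

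**Simulated rejection rates, lag-1 test against slope test:**

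| Cohorts | 2 SD | 3 SD | 4 SD |
|---|---|---|---|
| 6 | 2% vs 25% | under 1% vs 48% | under 1% vs 71% |
| 12 | 9% vs 50% | 20% vs 84% | 39% vs 97% |
| 17 | 13% vs 66% | 35% vs 94% | 63% vs nearly 100% |
| 24 | 19% vs 80% | 52% vs 99% | 83% vs 100% |

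With no drift, both tests reject in about 5 to 6% of runs. If the series is detrended first, the lag-1 test's rejection rate equals its size whatever the drift.

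**Other direction.** With no drift but lag-1 correlation of 0.5 between cohorts, an approximate lag-1 test (|r₁| above 1.96/√n) rejects in 10% of runs at 12 cohorts, 26% at 17 and 48% at 24. A rejection does not point to drift.

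**The case against.** The strongest reply is that the protocol names ARIMA regression models and no particular test. Such a model can carry a time or drift term, the phrase about autocorrelation trends is ambiguous, and model order and covariates are normally left to an analysis plan. That stands as far as the Ljung-Box form goes: it is my assumption. It does not remove the point, because the article does state what the models will test, in two places, and a time effect is named in neither.

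Calendar trend is also not among the objectives or the hypothesis. That is true, and it makes the analysis secondary. But the limitations section gives the models a job, and a test of serial dependence cannot do it.

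Looking at autocorrelation is not pointless. The same trainers deliver every session, and with a 3-month interval one cohort's post-test can coincide with the next cohort's pretest, so carry-over is plausible. This supports allowing for dependence in the errors; it does not make dependence the result of interest.

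Three stronger readings are tempting and unsupported. A reader might infer that any real drift would usually be missed; the table shows otherwise for 4 SD or more with 17 or more cohorts. A reader might infer that the main result depends on this test; the planned pre/post comparison is carried out whatever the ARIMA models show, and no passage makes pooling conditional on them. A reader might infer that a proper trend model would show the gain is due to the course; a calendar trend across cohorts says nothing about what each trainee would have learned anyway in the 3 months between tests.

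**Conclusion.** The point holds as a mismatch between the stated test and the use made of it. Autocorrelation is the only target named, while the limitations section relies on the models to overcome change over time. The test yields no trend in MCQ points and cannot separate drift from dependence. For moderate drift or short series it is also much weaker than a slope test: about 13% against 66% at 17 cohorts and 2 SD, and 20% against 84% at 12 cohorts and 3 SD. Those figures rest on linear drift, independent cohort means and a lag-1 test on the raw series. Linear drift with independent errors is the setting most favourable to the slope test. The conversion to points also rests on an assumed score SD and equal cadres. The mismatch itself needs none of these assumptions.

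**What to change.** In the Statistical analysis section and the abstract, state that pre score and gain will be regressed on session date by cadre, adjusting for site. The reported result should be the change in points per year with its 95% CI. Serial correlation or session clustering should be handled in the error structure or checked in the residuals. A regression with ARIMA errors and a reported time term would serve; a different class of model is not required.

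In the limitations section, drop the statement that autoregression models will overcome change over time, or limit it to the estimated calendar trend.

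The cost is three changed sentences. Score, session date, site and cadre are already part of the study's data. The downside is an assumed linear form for the trend, which can be checked with year indicators.
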